### Sample size calculation

For the a priori power analysis, GPower software v.3.0 (Heinrich-Heine-Universität, Düsseldorf, Germany) [28] was used to calculate the minimum sample size required for this study. Cohen’s effect size was randomly considered moderate to large (Cohen’s d = 0.65) according to decreased HADS-D and PHQ-9 scores when the experimental arms (A or B) were compared with the control group (Arm C). The estimated sample size would be 39 participants in each arm for a difference between independent means, α of 5% (two-tailed hypothesis) and a power of 80%. Each group shall have a total of 50 patients considering a monitoring loss rate of 25% to 30%. A study of this size will have 80% power to detect differences between Arms A plus B versus Arm C on the depression symptom scores associated with an effect size of 0.5 and alpha of 5%. This study is preliminary in nature, and a key objective of this study is to assess the feasibility and acceptability of a new clinical intervention. Furthermore, this study aims to assess the magnitude of the effect of adding a psychosocial intervention to early PC, which has not been determined according to the literature and would be useful in planning a future definitive phase III trial.

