### Data collection and randomization

The psychological intervention will be conducted by psychologists trained for the study. Data collection will be conducted by a team of research coordinators from the Center for Research Support at Barretos Cancer Hospital (BCH; Barretos, SP, Brazil).

A trained member of the Center for Research Support, not involved in data collection or statistical analysis, was assigned to handle the randomization process, using tables of random numbers. The study participants will be randomized (1:1:1) into arms A, B or C. Randomization will be based on blocks of six patients and will be stratified as follows: breast, gynecological, gastrointestinal, urological, head and neck, and thoracic. The study arms will be as follows:Arm A (experimental): psychosocial plus early PC, including five weekly psychosocial interventions based on CBT plus early PC (a first medical consult at the Palliative Care Service will be scheduled for 2 to 3 weeks from the study inclusion date and every 3 to 4 weeks thereafter).Arm B (experimental): early PC (a first medical consult at the Palliative Care Service will be scheduled for 2 to 3 weeks from the study inclusion date and every 3 to 4 weeks thereafter).Arm C (no intervention): standard oncologic care.

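### Fifty patients per arm leaves 35 to 37 evaluable at the stated 25% to 30% loss, just short of the 39 that the sample size calculation requires

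*Protocol article*

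**What the plan says.** The Sample size calculation section of the Protocol article assumes a Cohen's d of 0.65 on HADS-D and PHQ-9 for either experimental arm against the control arm. On that basis, "The estimated sample size would be 39 participants in each arm for a difference between independent means", with "α of 5% (two-tailed hypothesis) and a power of 80" percent. The section then moves from required to enrolled numbers in one step: "Each group shall have a total of 50 patients considering a monitoring loss rate of 25% to 30" percent. It shows no inflation formula and does not tie the loss rate to a visit.

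Three other places bear on the point:

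- Data collection and randomization fixes equal allocation: "The study participants will be randomized (1:1:1) into arms A, B or C".
- Primary outcome measures places the primary change in depression at day 90. Satisfaction and the secondary outcomes are followed to day 180.
- Early palliative care removes two groups from the statistical analyses: patients in Arms A and B with no palliative care session, and patients in Arm A who missed the first two psychosocial sessions.

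**The concern.** The only purpose of raising 39 to 50 is to have 39 left once the expected loss has occurred. Both ends of the stated loss range leave fewer than 39, so the required number, the loss rate and the enrolment figure cannot all stand.

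What is at stake is whether the power statement is true for the comparisons the trial was sized on, A versus C and B versus C. Depression at day 90 is a listed primary outcome, and the Statistical analysis section tests at P < 0.05. Someone reading the results, or planning the later phase III trial, will take 80% at d = 0.65 as what this design offered.

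**Working it through.** **Inputs, all from Sample size calculation except the allocation:** d = 0.65; two-sided alpha 0.05; power 80%; two independent means; 39 required per arm; 50 enrolled per arm; loss 25% to 30%. Allocation is 1:1:1 (Data collection and randomization).

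**Step 1: reproduce the 39.** For a two-sample t-test with n per arm, power is the probability that a noncentral t variable, with 2n − 2 degrees of freedom and noncentrality d × √(n/2), falls outside the two-sided 5% critical values. Solving for 80% power at d = 0.65 gives n = 38.14, rounded up to 39. At n = 39 the noncentrality is 0.65 × √19.5 = 2.87 and power is 80.9%. At n = 38 power is 79.9%, so 39 is the smallest whole number that reaches 80%. The normal approximation would give 38, so the plan's figure matches the t-test.

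**Step 2: apply the stated loss to 50.**

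- 25% loss: 50 × 0.75 = 37.5 evaluable per arm.
- 30% loss: 50 × 0.70 = 35 evaluable per arm.
- Largest loss that still leaves 39: 1 − 39/50 = 22%.

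**Step 3: compare two ways of allowing for loss.**

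| Loss | 39 ÷ (1 − loss) | 39 × (1 + loss) |
|---|---|---|
| 25% | 52.0, so 52 | 48.75 |
| 30% | 55.7, so 56 | 50.7 |

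The planned 50 lies inside the right-hand column's range and below the left-hand column's. Only the left-hand form leaves 39 after the loss.

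**Step 4: power at d = 0.65 with the numbers that remain (same t-test).**

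| Evaluable per arm | Noncentrality | Power | d detectable with 80% power |
|---|---|---|---|
| 39 | 2.87 | 80.9% | – |
| 37.5 (25% loss, unrounded) | 2.81 | 79.3% | 0.66 |
| 37 (25% loss, rounded down) | 2.80 | 78.8% | 0.66 |
| 35 (30% loss) | 2.72 | 76.4% | 0.68 |

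Against the stated 80%, the deficit is about 1 point at 25% loss (80 − 78.8 = 1.2, or 80 − 79.3 = 0.7 unrounded) and 80 − 76.4 = 3.6 points at 30%. In patients it is 39 − 37 = 2 per arm and 39 − 35 = 4 per arm.

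**The case against.** **The effect is tiny.** At 25% loss the deficit is about one point, and under the normal approximation 37.5 per arm would even give 80.4%. The 0.65 is itself an assumed value, so a shift of 0.01 to 0.03 in the detectable effect lies well within the uncertainty of that input. This stands as a comment on size. It does not reconcile the figures: the 39 comes from the t-test, and by that test power is below 80% across the whole stated loss range.

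**The study is preliminary.** Sample size calculation says so, and the Discussion names the small sample as the main limitation and ranks statistical significance below the main objectives. This limits the consequences. It does not make the power statement true, and nothing in the document says that fewer than 39 evaluable per arm is acceptable.

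**The loss rate has no time point.** If 25% to 30% means loss by day 180, loss by day 90 could be 22% or less and 39 would be met. This is fair, and the power figures are therefore conditional. Against it, the plan itself applies the rate to this calculation without any distinction between visits.

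**Stronger readings that the document does not support:**

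- A reader might infer that the exclusions described under Early palliative care come on top of the 25% to 30% and shrink Arms A and B further. The document does not say whether the loss rate includes them, and it gives no expected rate for them, so no further loss of power can be calculated.
- A reader might also take it as established that the allowance was made by multiplying instead of dividing. The figures fit that explanation, but no formula is shown, so it can only be said to appear so.

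**Conclusion.** The point holds as an internal arithmetic inconsistency of modest size. The requirement of 39 is right; enrolling 50 per arm preserves it only up to 22% loss, and the plan expects 25% to 30%. Power for each experimental arm against control is then about 76% to 79% instead of 80%.

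This rests on three assumptions: that the stated loss applies to the day 90 comparison, that it falls equally on the arms, and that the analysis is the two-sample comparison on which the 39 is based. It does not show that the trial is seriously underpowered, and it gives no reason by itself to change the enrolment target or the analysis population. Whether the exclusions from analysis are appropriate is a separate question that this correction does not need to settle.

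**What to change.** Keep 50 per arm and replace the sentence on loss with wording such as:

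> Fifty per arm gives 39 evaluable if loss is at most 22%; at the anticipated 25% to 30% loss (35 to 37 evaluable) power at d = 0.65 is about 76% to 79%.

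Add a clause saying whether the 25% to 30% includes the patients removed from analysis under Early palliative care, and whether it refers to day 90 or to day 180.

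The cost is a sentence or two and a slightly less favourable power figure. The alternative, holding 80% power at the stated loss, needs 52 to 56 per arm. That is 156 to 168 patients against the planned 3 × 50 = 150, or 6 to 18 more. For a shortfall of this size in a trial already enrolling, restating the power is the proportionate choice.

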### Monitoring committee

An independent monitoring committee that consists of staff from the Center for Research Support (Coordenadores de Pesquisa do Núcleo de Apoio ao Pesquisador, NAP) of BCH will monitor the collection and analysis of the study data.

### Interim data analysis

An interim analysis is planned for 90 days after the inclusion of 20 participants with complete data in each arm. If Cohen’s effect size between Arms A and B is <0.2 the authors will consider ways to strengthen the psychosocial intervention.

### Ethical aspects

All of the individuals who meet the inclusion criteria will be invited to participate in the study. Each participant will voluntarily sign an informed consent form. The research protocol for this study was developed according to the standards of the National Health Council Resolution number 466/12 and the guidelines of the Declaration of Helsinki. The study protocol was approved by the Research Ethics Committee of the Barretos Cancer Hospital (n° 699/014).

## Discussion

The feasibility and impact of a brief psychosocial and educational strategy, which is based on CBT, will be evaluated in patients with advanced cancer who start palliative chemotherapy to determine whether the patients will be in a better condition when assessed for the first time by a PC team. We believe that the benefits of psychological intervention shall be synergistic to secondary emotional benefits from the early integration of PC. Therefore, this study will evaluate a new strategy for the transition into PC. Furthermore, the inclusion of early PC with or without a brief psychosocial and educational strategy will be compared to standard oncological care in a control arm (first-line palliative chemotherapy) in which patients are referred to PC by the attending physician.

Identifying the reasons patients are referred to PC services is essential because of the benefits of early PC in patients with advanced cancer [6-8,29]. Patients are most likely referred to PC too late even at oncology reference centers [9]. Two randomized phase III trials [6,7] found that early PC was associated with lower levels of depression symptoms compared with standard oncologic treatment. This study aims to confirm this benefit and to examine whether the psychosocial and educational strategy can reduce depression symptoms over time. This original approach may be useful in hospitals with settings similar to those at BCH. This large hospital is dedicated exclusively to oncology and has a well-structured PC service; however, this service is associated with significant patient stigmatization. Patients often perceive the PC unit as being exclusively for dying patients, which complicates their acceptance of early referral to PC.

The attribution of meaning is important for detecting maladaptive behaviors, which are modifiable through interventions according to CBT [30]. CBT is based on the premise that cognition affects behavior; however, cognition may be monitored and changed and the desired behavioral change may be achieved through cognitive change [31]. CBT aims to enable individuals to identify and modify their distorted or dysfunctional automatic thoughts [32]. Evidence suggests that CBT may benefit advanced-stage cancer patients by reducing anxiety symptoms, improving QL [33], and decreasing psychiatric disorders, which have been observed in cancer patients who were classified as high-risk for the development of such disorders [25]. Therefore, the study population in the present study (advanced-stage cancer patients who start palliative chemotherapy) may be considered at a high risk for developing depression. Psychoeducation is another key tool used in CBT. In a previous clinical trial, cancer patients were submitted to a psychoeducational intervention. This strategy was effective in improving disease awareness rates, and the patients were better equipped to deal with problems, had lower levels of isolation and guilt, and felt a sense of belonging to the group. A broad sharing of experiences and lessons by other patients with advanced cancer was observed [34].

The strategy that has been proposed in this study is novel and has not yet been assessed in this context. BCH receives patients from all of the states in Brazil, particularly patients from the Southeast, Midwest and North regions because this hospital is recognized as a reference institution in the Brazilian public health system. Despite being monocentric, this study will assess the impact of the intervention in a culturally heterogeneous population with different needs, and the results of this study may be generalized to the entire Brazilian population.

The study has several limitations and challenges. The main limitation is the small sample size. This study is preliminary and will assess the feasibility of a new intervention and provide initial data on the magnitude of its benefit. Therefore, the statistical significance of this intervention is less important than the main objectives of the study. A larger confirmatory study may be necessary depending on the results of this phase II study. This study will include patients without underlying psychological problems. We anticipate difficulties in enrolling patients because many advanced cancer patients receive psychological support and use antidepressants as part of standard care. Another difficulty in enrolling patients may be the stigma regarding the PC unit and psychological approaches. However, those difficulties will be analyzed in the feasibility assessment.

## Trial status

Patient enrollment in the study began in August 2014. The last patient is expected to be included in January 2017.

## Abbreviations

BCH: Barretos Cancer Hospital
CBT: cognitive behavioral therapy
ECOG-PS: Eastern Cooperative Oncology Group performance status
ESAS-Br: Brazilian version of the Edmonton Symptom Assessment System
FAMCARE: Family Satisfaction with End-of-life Care
HADS: Hospital Anxiety and Depression Scale
PC: Palliative Care
PHQ-9: Patient Health Questionnaire
PREPArE trial: Pre-palliative Emotional Care Trial
QL: quality of life
